**8. Participant Retention**

At enrolment, all participants will be asked to provide detailed locator information. Specifically, participants will be asked to provide their full name, address and contact numbers (including landline and cellphone). In addition, the names, addresses and contact details of two individuals with whom the participant lives and one individual with whom the participant does not live will be requested. Participants will be asked to update their locator information at all subsequent visits as necessary. All locator information will be kept in locked study cabinets accessible only under the direction of the study coordinator.

After enrolment, all study activities will take place through appointments conducted separately from the ART care provided at the clinic or clubs. All participants will receive reminder calls one day prior to their scheduled study visit.

There will be two main approaches to tracing participants who miss study appointments:

- Telephonic contact with the participant or with an alternate individual pre-designated by the participant will be attempted.
- If telephone attempts fail, study fieldworkers will visit the home address of the participant to trace the participant in person.

All participant tracing efforts by any staff (via phone or home visit) will not mention the reason for the contact, or anything regarding HIV/AIDS or ART. All contacts simply request that the participant come to the clinic the next working day for a health-related issue. Our research team has been working in this setting for more than 8 years, has close knowledge of the local community, and has extensive experience with retention activities around HIV/AIDS.

As part of research activities, we will include an assessment of whether the participant is taking ART. For those individuals found not to be using ART, staff will facilitate an urgent referral back to the appropriate services as per randomization assignment. Details and examples of these retention procedures, including the adherence assessment, will be included in the staff training to be conducted prior to study implementation.

Participant withdrawal

All participants may refuse or voluntarily withdraw from the study for any reason and at any time. As part of the informed consent process, staff will state specifically that participation in the study is voluntary and that a participant may refuse participation or withdraw from study participation at any time. Participants will be told that withdrawal from the study will have no effect on their access to health facilities or HIV-related testing, care and treatment services. All study staff will be trained to ensure that participants have a firm understanding of this concept at the time of the informed consent process; per consenting requirements, the informed consent form will also include a statement to this effect.

**9. Analytic considerations**

Sample size considerations

The projected sample size for the trial is 214 participants

This estimate is based on the following assumptions:

- A superiority comparison of the immediate and delayed club referrals.
- 90% power and a two-sided alpha of 0.05 using a log-rank test of survival proportions
- 1:1 randomization
- An expected proportion of virally suppressed adults in the delayed referral group of 65% (our best estimate of this is 68% from data collected at Gugulethu) and an expected proportion of adults in the early referral group of 85%. Thus the expected minimum difference in the primary outcome at 12 months post-initiation between the early and delayed arms is 20%.
- Furthermore, the proposed sample size will also provide >80% power to detect appreciable differences for most secondary outcomes of interest.

Data management

Data management will be as for the PACART study based at UCT and Gugulethu. Data collected on paper forms will be entered into a custom designed Microsoft Access database, maintained in a firewall-protected UCT server with nightly backups. The study database will be password-protected following standard password safety procedures. The database will be designed and maintained by a senior data manager who will develop the data dictionary, direct queries, and data quality assurance / quality control activities, and will supervise the data entry clerk. Data quality assurance will be in the form of robust database structure and platform, “front-end” data checks, including real-time database queries. Quality control will be through data checking scripts to identify out-of-range values, logic violations, and missing observations. Data editing will be based on reference to the form and/or source document in question; all data queries and responses will be logged, and edits will be implemented through separate program files. All study records will contain anonymous participant identification numbers, and no participant names or identifiers will be recorded.

Data analysis

Data will be exported to Stata Version 13.0 (Stata Corporation, College Station, Texas) or R (Gnu Project) for analysis. The full statistical analysis plan will be developed by the trial statistician as per the PACART trial. Here we provide a brief outline of planned analyses.

For the **primary objective**, we hypothesize that adults randomized to early club referral will be more likely to maintain viral suppression (defined as <400 copies/ml, with secondary analyses at other thresholds) up to 12 months post-ART initiation, compared to adults randomized to delayed club referral.

Comparisons of study arms at enrolment will examine demographic, clinical and relevant behavioural variables. Primary analyses will be by intention-to-treat in participants with a VL <400 copies/mL. Secondary ‘per protocol’ analyses will be based on actual attendance at least one visit at the intended service. Additive binomial regression models will be used to assess the effect of trial arm on the primary outcome, with results presented as absolute risk differences with 95% confidence intervals. Models will be adjusted for clinical and demographic characteristics thought to predict the outcome while not mediating the intervention effect. Intervention effects will be examined across *a priori* subgroups including age, gender, previous antiretroviral exposure and nadir CD4 cell count.

For the **secondary objectives**, we hypothesize that adults randomized to early club referral will be more likely to be retained in care (defined as attending ART clinical appointments as scheduled), compared to adults randomised to delayed club referral. Analyses of other secondary outcomes (including measures of health status and health service utilization, as well as quantitative acceptability measures) will be based on pure-count methods, beginning with a description of variables overall and by arm using proportions with exact 95% confidence intervals, or median with interquartile ranges. Comparisons of distributions by trial arm will employ exact tests or rank-sum tests, as appropriate. Throughout statistical tests will be 2-sided at α=0.05, with the exception of primary outcome analyses that will be adjusted for interim looks (see below). Generalized linear models will be used to examine multivariable prediction of outcomes of interest. Models with repeated outcomes per subject over time will account for within-subject correlation through subject-specific random effects. Model fit will be compared using AIC and LR statistics; all modelling will employ standard diagnostic procedures.

Interim analyses

The Data Monitoring Committee will monitor trial progress and conduct periodic reviews of the trial outcomes. This independent review will be valuable in maximizing the benefits of the trial findings for scientific and policymaking purposes. The DMC will review: (i) the rate of recruitment; (ii) any adverse events identified during the study including social adverse events; and (iii) evidence for the primary outcome (viral suppression) including evidence for superiority or inferiority. On advice from the Trial Steering Committee, we propose that stopping rules be provided to the DMC only as guidelines to help assist in any decision making around stopping the trial due to evidence of inferiority or superiority in the primary outcome

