Locally, implementation of these clubs has been found to be generally successful and popular with clinic staff and patients, with one local study describing a period of 18 months during which a third of clinic patients were de-centralized to clubs.^10^ Overall ART retention in this study was found to be 97.2% at 6 months (95% CI=95.4-97.8) and 93.5% (95%CI=92.2-94.5) at 12 months, and after a year in a club more than 98% of patients remained virally suppressed.^10^ Although there was no suitable comparison group in this study, these retention rates were shown to be well above the estimated retention rates described above and so this study supported continued expansion of the clubs model.

Analytical studies have shown that local adherence clubs decrease both loss-to-follow-up (hazard ratio 0.43, 95% CI=0.21-0.91) and viral rebound (hazard ratio 0.33, 95% CI=0.16-0.67) compared with usual clinic care.^5^ A later study confirmed this association, finding a loss-to-follow-up hazard ratio of 0.33 (95% CI=0.27-0.40) when comparing club care with clinic care.^11^ These comparative studies add more support in favour of the roll-out of the club model.

Adherence clubs have also been shown to be more cost-effective than clinic care, in low- and middle-income countries^9^ and also locally, with one study estimating a cost per patient-year of $300 for clubs vs $374 for clinic care.^12^ Interviewed club patients reported a higher acceptability of club compared to clinic as well as shorter waiting times.^12^ Again this study concluded by supporting scale-up.

So whilst adherence clubs have been shown to be locally implementable, popular (with buy-in by clinic staff and patients) and cost-effective, and community-based interventions have been shown to improve retention, evidence of local adherence club effectiveness in improving viral suppression and retention has only been observationally obtained.^6^ This observational evidence is highly subject to selection bias, with already-adherent patients being over-represented in the club system because of the club eligibility criteria, which includes a suppressed viral load. Even if this selection bias is limited by including viral suppression as a study eligibility criteria, there still remains the possibility of residual confounding in patient factors such as an openness to club-based care and more inherent adherence.^5^

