**7. Research Procedures**

Randomisation

Randomisation will be performed once enrolment is completed. Randomization will be a 1:1 allocation using a dynamic permuted block design generated by an independent statistician. Randomization numbers will be generated prior to the start of the study, and placed in sequentially numbered opaque envelopes. Randomization envelopes will be stored in a locked and restricted access cabinet in the research clinic that will be accessed by the study coordinator when a participant is fully consented and has been enrolled in the study. There will be independent documentation of the participant identification number, randomization date, and randomization assignment. The study coordinator involved in randomization will not be involved in interviewing participants. The allocation to either early or delayed adherence club referral will be conveyed to both the participant and to the study recruiter.

Early referral arm

The participant will be escorted by study staff straight from enrolment to the club office for referral to the club service. Here, a club counsellor will educate them about the club system and rules, enrol them into a club and give them a club appointment date within 2 months. If more ART will be needed before the date is reached, a study clinician will dispense. The specific club group to which the individual is assigned will depend on space availability within groups. Participants will be allocated to groups non-purposively, and there will be no attempt to cluster participants within a single group. Their clinic appointment, in 1 months’ time for viral load results, will be cancelled.

Delayed referral arm

Individuals randomized to this arm will be seen at the clinic, with no club referral to be done before 12 months post-initiation. After 12 months has elapsed after initiation, the participant will be subject to usual clinic procedures which may include referral to clubs, dependent on the attending clinician as per standard of care.

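### The secondary per-protocol rule is a post-randomisation filter that acts mainly on the early arm and can tilt that estimate towards clubs; a complier-average risk difference would serve better

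*Combined protocol and SAP*

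**What the plan says.** Section 9 (Data analysis) sets the primary set: "Primary analyses will be by intention-to-treat in participants with a VL <400 copies/mL". It then adds secondary per-protocol analyses, and the whole definition is that these "analyses will be based on actual attendance at least one visit at the intended service". It gives no time window and no condition on attending the other service. It does not say whether a clinic visit before randomisation counts. Adjustment is for clinical and demographic characteristics. The section describes itself as a brief outline, with a full SAP to follow.

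Section 7 fixes the intended service in each arm. Early-arm participants are escorted to the club office at enrolment, where a counsellor will enrol them and "give them a club appointment date within 2 months"; their clinic appointment is cancelled. Delayed-arm participants stay at the clinic, with "no club referral to be done before 12 months post-initiation". A folder sticker and a list held at the club office are meant to enforce this. Section 5 shows that everyone leaves the month-4 visit with a clinic date one month ahead, and Section 7 cancels it only for the early arm.

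**The concern.** The same words set a different hurdle in each arm. An early-arm participant qualifies only by turning up at a service they have not used before, after randomisation. A delayed-arm participant qualifies by returning once, at any time in follow-up, to a clinic they already attend. The exclusions should therefore fall mainly on the early arm. Failing to appear at a first club session is plausibly related to adherence, which drives viral load.

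Section 1 names openness to club care and inherent adherence as residual confounders in the observational studies. A set chosen by club attendance lets both back into this secondary comparison, and adjustment for clinical and demographic characteristics need not remove them. At stake is a secondary estimate that could look larger than the intention-to-treat result for reasons unrelated to clubs.

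A separate gap is that a delayed-arm participant who attends the clinic once and then joins a club before 12 months still counts as per protocol.

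**Working it through.** **The plan's own figure.** Section 9 assumes "An expected proportion of virally suppressed adults in the delayed referral group of 65"% and 85% in the early group, "1:1 randomization" and "90% power and a two-sided alpha of 0.05 using a log-rank test of survival proportions", giving 214.
- Continuity-corrected comparison of two proportions: 107 per arm, 214 in total.
- Log-rank (Freedman): hazard ratio ln(0.85)/ln(0.65) = 0.377, 52 events; 52/0.25 = 208, within 3% of 214.

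The sample size is not at issue. It supplies the 20-point yardstick and the 107 per arm used below.

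**Formula for the filter.** Let both arms have true suppression p (no effect). If a share f of an arm is dropped and those dropped have suppression q, the retained rate is (p - f x q)/(1 - f). The documents give no f or q, so all values below are assumptions.

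**Illustration: p = 0.75, q = 0.40.**
- Early arm, f = 0.10: (0.75 - 0.10 x 0.40)/0.90 = 0.789
- Early arm, f = 0.15: (0.75 - 0.15 x 0.40)/0.85 = 0.812
- Delayed arm, f = 0.03: (0.75 - 0.03 x 0.40)/0.97 = 0.761
- False gain for early referral: 0.789 - 0.761 = +2.8 points; 0.812 - 0.761 = +5.1 points

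That is 14% to 26% of the 20-point design difference (2.8/20; 5.1/20).

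**Wider range: p = 0.65 (the delayed-arm planning rate), nobody dropped from the delayed arm.**

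| Early arm not linking | Suppressed among them | Retained early rate | False gain (points) | Two-sided 5% test rejects |
|---|---|---|---|---|
| 5% | 50% | 65.8% | +0.8 | 5.2% |
| 10% | 30% | 68.9% | +3.9 | 9.0% |
| 20% | 20% | 76.2% | +11.2 | 39% |

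**Lower limit.** If non-linkers resemble everyone else, q = p and (p - f x p)/(1 - f) = p. There is then no bias at any f.

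**Crossover in the delayed arm.** Suppose 5-20% enter a club early and reach 85%.
- Kept in: the delayed rate becomes 0.95 x 0.65 + 0.05 x 0.85 = 0.66, or 0.80 x 0.65 + 0.20 x 0.85 = 0.69. The 20-point difference shrinks to 19 or 16 points, which is dilution towards zero.
- Excluded, with no club effect and crossovers 85% suppressed: (0.65 - 0.05 x 0.85)/0.95 = 0.639, or (0.65 - 0.20 x 0.85)/0.80 = 0.600. That is a further false gain of 1.1 or 5.0 points for clubs.

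**Complier-average estimate.** This is the intention-to-treat risk difference divided by the between-arm difference in the proportion attending a club before study visit 3. With no true effect the numerator is 0, so the estimate is 0 whatever the linkage rate, because nobody is dropped. With 10-15% non-linkage and no crossover the divisor is 0.90 to 0.85. Treating it as fixed, the interval widens by a factor of 1/0.90 = 1.11 to 1.17-1.18 (1/0.85).

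**The case against.** The strongest reply is that little rests on this analysis. It is explicitly secondary, the primary comparison is intention-to-treat, and a full SAP is still to come. That stands, and it limits the point to one secondary estimate.

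The protocol also works to keep non-linkage low. Participants are escorted to the club office and enrolled there, with ART dispensed by a study clinician if it is needed before the first date. Section 4 requires willingness to attend either service, and participants found non-adherent are referred back to their assigned service (Sections 7, 8 and 10). These steps should shrink the bias, but they do not make the rule symmetric. Even +2.8 to +5.1 points is only about 0.5 to 0.9 of a standard error (about 6 points with 91 to 104 per arm).

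The filter is not one-sided by definition either. A delayed-arm participant who never returns to the clinic is also dropped, unless the pre-randomisation visit counts.

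Three stronger readings are tempting, and the documents do not support them.
- A reader might infer that the trial as a whole regains the selection bias it was designed to avoid. It does not, because the randomised primary comparison is intact. Section 1 does say "This observational evidence is highly subject to selection bias, with already-adherent patients being over-represented in the club system", but it attributes this to club eligibility criteria that include a suppressed viral load. Here both arms meet the same month-4 suppression criterion.
- A reader might infer that keeping delayed-arm club entrants adds to the pro-club bias. If clubs work, it pulls the difference the other way, and the sticker and club-office list should make such entry uncommon.
- A reader might infer that those entrants should be excluded. That is another post-randomisation selection, and the calculation above shows that it can favour clubs further.

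A complier-average estimate has its own weakness. It assumes that allocation affects viral load only through club attendance. Cancelling the early arm's clinic appointment could affect people who never reach a club. Section 7 (Contamination and masking) also allows that awareness of the other arm may change behaviour.

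**Conclusion.** The point holds for the secondary per-protocol analysis only. As written, the rule selects after randomisation, mainly in the early arm, on something plausibly related to adherence, so its estimate can lean towards clubs. The size cannot be fixed from the documents. It is +2.8 to +5.1 points under the stated illustration, +0.8 to +11.2 points over the wider assumed range, and near zero if non-linkers are like the rest. The direction depends on non-linkers being less often suppressed. The failure to detect early club entry in the delayed arm is a separate gap that works towards zero, so the net direction is not certain if crossover is common. This merits a change before the SAP is final, but it does not threaten the primary conclusion.

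**What to change.** Keep intention-to-treat as primary. In the full SAP, make the main secondary adherence-related analysis a complier-average risk difference with a 95% CI, using randomisation as the instrument: the intention-to-treat risk difference divided by the between-arm difference in the proportion attending a club before study visit 3. State the exclusion restriction, and say that cancelling the early arm's clinic appointment may strain it.

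If the one-visit analysis is kept:
- label it non-randomised and descriptive;
- define the intended service and the time window, and count only post-randomisation visits in both arms;
- report linkage and crossover by arm;
- do not exclude delayed-arm crossovers.

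The cost is SAP wording. Section 7 (Data abstraction) already collects dates of routine visits attended, from clinic and club records as needed. The downside is reliance on the exclusion restriction and a somewhat wider interval.

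### The adjusted identity-link binomial model for the primary outcome has no stated CI method or fallback, and with several covariates at N=214 it would often have no interior solution

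*Combined protocol and SAP*

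**What the plan says.** The analysis text is in section 9 of the combined protocol and SAP, under Data analysis. For the primary outcome (viral load below 400 copies/ml up to 12 months after ART initiation) it states: "Additive binomial regression models will be used to assess the effect of trial arm on the primary outcome". Results are to be given as absolute risk differences with 95% intervals. It then states: "Models will be adjusted for clinical and demographic characteristics thought to predict the outcome while not mediating the intervention effect".

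Age, gender, previous antiretroviral exposure and nadir CD4 count appear in the same paragraph, but as subgroups and not as adjustment variables. The section does not give the number, identity or coding of the covariates. It does not say whether the adjusted or the unadjusted estimate is primary, how the interval is computed, or what happens if the model cannot be fitted. There is a general promise of the usual model checks. The section describes itself as an outline and defers to a complete analysis plan to be written later.

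On size, under Sample size considerations: "The projected sample size for the trial is 214 participants", for 65% suppression in the delayed arm and 85% in the early arm.

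**The concern.** With an identity link the linear predictor is itself the risk, so every participant's fitted value must lie between 0 and 1. The early arm starts at an expected 85%, which leaves 15 percentage points for all covariates together. If the likelihood is maximised where some fitted risk reaches 1, standard software fails to converge or stops on the boundary. The usual standard error theory does not apply there.

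What is at stake is the interval for the primary result. With no fallback written down, the analyst must decide what to do after seeing the fit fail, or may report a Wald interval that the theory does not support.

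**Working it through.** **Inputs from section 9.** N = 214, allocated 1:1 (107 per arm); suppression 65% (delayed) and 85% (early); additive binomial model; adjustment for unlisted characteristics. The local estimate for the delayed arm is 68%, and it was run as an alternative. No dropout allowance is stated, so none was used.

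**The plan's own figure.** The uncorrected two-proportion formula, with mean risk 0.75 and difference 0.20, gives

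n = [1.960·√(2·0.75·0.25) + 1.282·√(0.65·0.35 + 0.85·0.15)]² / 0.20² = (1.200 + 0.764)² / 0.04 ≈ 96.4 per arm, so 97 per arm (194 in total).

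With the continuity correction, (96.4/4)·[1 + √(1 + 4/(96.4·0.20))]² ≈ 106.2, so 107 per arm and **214** in total. The stated size is reproduced. The log-rank test that the plan names gives 208 (Freedman) or 180 (Schoenfeld). The point here does not depend on which was used.

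**Why the boundary is close.** Take one continuous covariate with an assumed odds ratio of 1.5 per SD. The average of p(1−p) over the arms is (0.2275 + 0.1275)/2 = 0.1775. The slope on the risk scale is then about ln(1.5)·0.1775 = 0.405·0.1775 = 0.072 per SD. The 15-point headroom in the early arm is used up at 0.15/0.072 ≈ 2.1 SD. About 1.9% of a normal distribution lies beyond that, or about 107·0.019 ≈ 2 early-arm participants. A single such fitted value is enough.

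**Simulation.** 1,000 trials per scenario (500 with eight covariates), N = 214, 65% versus 85%. The log-likelihood is concave and was maximised on its open domain. A trial counts as having no interior solution if any fitted risk at the optimum lies outside (0,1) or the optimum is not reached. Assumptions not in the documents: age and CD4 standard normal; 35% in one gender category; 12% with previous ART exposure; covariate odds ratios of 1.0, 1.5 or 2.0 per SD or level.

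| Adjustment set | OR 1.0 | OR 1.5 | OR 2.0 |
|---|---|---|---|
| None | 0% | – | – |
| One binary | 0.2% | 1.5% | 2.8% |
| Two binary | 13% | 9% | 10% |
| One continuous | 8% | 52% | 84% |
| Four subgroup factors, all dichotomised | 31% | 36% | 50% |
| Four subgroup factors, age and CD4 continuous | 44% | 93% | 99% |
| Eight mixed | 84% | 100% | 100% |

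Monte Carlo standard error is at most about 2 points. Using 68% for the delayed arm, or 85% in both arms, changes little: with four mixed covariates, 44-99% and 51-100%. Further simulations with other assumed effect sizes gave 23-47% for the dichotomised set and 43-92% for the mixed set. If the truth is exactly additive, with four binary covariates worth 5 points each, the share is still 33%.

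**Consequence for the interval.** Where an interior solution exists, Wald coverage is about 93-95%. In boundary fits with continuous predictive covariates, the ordinary Wald interval covered about 70-90% (lowest 68%).

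**Alternatives on the same scale.** Logistic standardisation gave 94-96% coverage, had power about equal to the unadjusted comparison, and failed to fit in 6 of 7,200 trials (0.08%). A linear probability model with robust standard errors always fitted, with 95-97% coverage.

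**The case against.** The strongest reply is that the failure rate comes from assumptions and not from the plan. The four factors are named only as subgroups, and with no covariates or one binary covariate the problem is absent or negligible. This stands, and it is why the result is a range. On the other hand, the plan speaks of clinical and demographic characteristics in the plural, chosen because they predict the outcome, and predictive covariates mostly raise the rate.

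A second reply is that the text is an outline and a fuller plan will settle covariates, interval and fallback. This lowers the weight of the point. But the outline already fixes the model family and the adjustment, so a later plan that follows it inherits the difficulty. The general promise of model checks names no remedy.

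Third, a reader might infer that dropping covariates until the model converges would distort the result. The documents do not say that this would be done. In simulations that dropped covariates in a fixed order, coverage was 92-95%, bias was at most 0.6 percentage points and type I error was 4-6%. Randomisation explains this: omitting a baseline covariate does not bias the comparison of arms. Those runs do not cover choosing covariates after seeing the results.

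**Conclusion.** The point holds as a conditional one. The planned adjusted model, used with several covariates at this sample size, would often have no interior solution: roughly 25-50% of trials with the four subgroup factors dichotomised, and 45-99% with age and CD4 continuous. No method is given for the interval in that case. The figures rest on the assumed covariate set, its distributions and its effect sizes. Across all sets examined, the range is 0% to 100%.

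A reader might go further and conclude that the primary estimate or its interval will not exist, or that the trial's main result will be invalid. The documents do not support that. The text does not say that the adjusted estimate is the primary one, and the unadjusted additive model always had an interior solution. A boundary fit still gives a constrained estimate; what is lost is ordinary convergence and the justification for the Wald interval. Nor is suppression expected near 85% throughout: that is the early arm only, and the average over the two arms is (65 + 85)/2 = 75%.

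This should be corrected before analysis. It does not call the design or the sample size into question.

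**What to change.** Keep the absolute risk difference. In the SAP, before the arm codes are broken:

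- Fix the list and coding of baseline covariates. The four subgroup factors are a natural candidate set.
- Obtain the adjusted estimate by standardisation (g-computation): fit a logistic model with arm and these covariates, average the predicted risks with everyone set to each arm in turn, and take the difference with a robust or delta-method 95% CI. A linear probability model with robust standard errors is an acceptable equivalent.
- Name this one estimate as primary, and report the unadjusted risk difference as supporting.

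The cost is a paragraph of SAP wording and a few lines of Stata or R. Data collection, N and effect measure do not change.
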